**Methods/Design:**

A two-armed, randomised controlled trial with blinded outcome assessment will be conducted to evaluate the comparative effectiveness of two modes of care, including a Usual Care Group and a Cardiac-Diabetes Transcare Intervention (in addition to usual care) Group. The primary outcome is 6-month readmission rate, although a range of secondary outcomes will be collected (including self-efficacy) at baseline, 1, 3 and 6 month reassessments. The intervention group will receive in-hospital education tailored for people recovering from an acute coronary syndrome-related hospital admission who have comorbid diabetes, and they will also receive home visits and telephone follow-up by a trained Research Nurse to reinforce and facilitate disease-management-related behaviour change. Both groups will receive usual care interventions offered or referred from participating hospital facilities. A sample size of 432 participants from participating hospitals in the Australian states of Queensland and Victoria will be recruited for 90% power based on the most conservative scenarios modelled for sample size estimates.

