### Sample size considerations

A target sample of 432 patients (with an anticipated attrition rate of 20% over the 6 month follow-up period) will be recruited from participating hospital facilities in Australia. The participating hospitals include the Royal Brisbane and Women’s Hospital (929-bed tertiary referral public hospital, located in Brisbane, Queensland, Australia), and the St Vincent’s Hospital, Melbourne (504-bed tertiary referral metropolitan hospital, located in Melbourne, Australia).

Completed data on 173 patients per group will enable over 90% power to detect 17.5% difference between groups in 6-month readmission rate (30% versus 47.5%) with alpha = 0.05. The assumptions for this sample size calculation were based on a more conservative anticipated effect than the large effect observed in a subgroup of patients (*n* = 49) with comorbid cardiac condition and diabetes from a randomised trial previously conducted by investigators of the present trial [8]. The previous study similarly included an intervention comprising a home visit and 6-month follow up, but was not tailored for patients with dual ACS and type 2 diabetes and instead targeted older adults who had been hospitalised. The sub-group analysis indicated a large effect of the intervention resulting in a 31.5% (intervention 25.0% versus usual care 56.5%) between group differences in raw 6-month readmission rates.

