### Randomisation, concealment and group allocation

A computerised random number sequence generated by an independent statistician (not involved in the day-to-day trial) will be used to allocate each participant to the control or intervention group in a one-to-one ratio. Group allocation is concealed in opaque envelopes that stored in a lockable filing cabinet accessible to a randomisation gatekeeper (an administration officer not otherwise involved in the conduct of the trial). After a patient has been recruited, the member of the research team responsible for co-ordinating intervention allocation will telephone the randomisation gatekeeper to reveal the group to which that participant has been allocated. Group allocation will then only be known by the randomisation gatekeeper, the person responsible for the intervention allocation and those providing the intervention (ResN) at each participating site. Participants will not be directly told their group allocation (in terms of usual care or intervention). Control group participants will continue to receive the usual standard care while participants in the intervention group will receive usual care as well as the Cardiac-Diabetes Transcare Program.

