#### Measures

Outcome measures will include: The primary outcome for effectiveness is readmission to hospital, as recorded in patients’ medical record, hospital administrative records, or patient report of readmission to a non-participating hospital (e.g. while travelling). Secondary outcomes include health status (e.g. blood pressure, blood glucose levels documented on the medical record), Assessment of Quality of Life (AQoL) [20] for health-related quality of life, Self-efficacy for Managing Chronic Disease 6-item Scale [21] for self-management, Medical Outcomes Study Social Support Survey [22] for psychosocial well-being, Patient self-report for Health Service Utilisation Questionnaire [23] as well as Medicare and Pharmaceutical Benefits Scheme claims information, and hospital administrative data for healthcare related resource usage to which healthcare costs will be attributed.

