### Data analysis

Data analysis will be conducted using intention-to-treat principles. The following analyses will be undertaken:Baseline data for both the intervention and control groups will be examined to check for similarity of the groups. Variables with potential differences between groups at baseline will be controlled for during subsequent analyses.Comparisons between groups will be undertaken to examine the effect of being allocated to the intervention versus control group on the primary and secondary outcomes using generalised linear mixed modelling. These analyses will be adjusted for age and gender in addition to any variables with potential between group differences identified at baseline.Healthcare costs (healthcare system and intervention-related costs) over the 6-month follow-up will be summarised for control and intervention group participants.A trial based economic evaluation will also be conducted alongside the randomised controlled trial (RCT) to quantify the additional costs (or cost savings) per health benefit (Quality Adjusted Life Years (QALYs)) attributable to the intervention in comparison to usual care alone. This will be expressed in the form of an incremental cost effectiveness ratio. All costs will be measured in Australian dollars for the year of study completion. Bootstrap re-sampling of trial data will be used to construct 95% confidence ellipses and cost-effectiveness acceptability curves will be prepared. Sensitivity analyses will be conducted to examine the robustness of these estimates to change in cost, effect, time-horizon, and background context data.

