Our previous randomised controlled trials undertaken in a general medical population of hospitalised older adults have demonstrated significant reductions in readmissions, improved quality of life and cost effectiveness through implementation of a theory based intervention comprising home visit and telephone follow up after discharge from hospital [8, 30]. Additionally, our previous work has addressed a number of gaps in the literature regarding needs of ACS patients with type 2 diabetes, and we have piloted cardiac-diabetes self-management programs in preparation for the present trial. Results from this preparatory work have demonstrated the feasibility of the program and a favourable effect on patient self-efficacy [12]. This proposed study builds on previous work through delivering an intervention prepared with a multidisciplinary team, to be evaluated in a randomised controlled trial across two states in Australia to evaluate the clinical and cost effectiveness of this cardiac-diabetes TRANSCARE program.

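### The primary outcome is powered as a single 6-month proportion but assigned a mixed model, and hospital is not among the named covariates; a fixed-effect binary regression including hospital would be a cost-free improvement

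*Protocol article*

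**What the plan says.** The Data analysis section of the protocol article applies one model class to every endpoint. The groups are compared "on the primary and secondary outcomes using generalised linear mixed modelling". No random effect is named. On covariates it says: "These analyses will be adjusted for age and gender in addition to any variables with potential between group differences identified at baseline".

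The abstract states: "The primary outcome is 6-month readmission rate". The Measures section says: "The primary outcome for effectiveness is readmission to hospital, as recorded in patients’ medical record". It does not say whether this is a yes/no variable or a count. The sample-size section gives over 90% power, with 173 completers per group, for a "17.5% difference between groups in 6-month readmission rate (30% versus 47.5"%), which is one proportion per arm. That section names two hospitals, one in Brisbane and one in Melbourne. Its wording does not rule out others, but none is named.

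The abstract attaches the repeated schedule to the secondary endpoints: "a range of secondary outcomes will be collected (including self-efficacy) at baseline, 1, 3 and 6 month reassessments".

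On allocation, a computerised sequence "will be used to allocate each participant to the control or intervention group in a one-to-one ratio". The section does not mention hospital. The Discussion describes the program as "to be evaluated in a randomised controlled trial across two states in Australia".

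**The concern.** A generalised linear mixed model needs at least one random effect. The article offers two natural grouping levels, patient and hospital. Neither suits an outcome with one yes/no value per patient from two hospitals. A patient variance has nothing to be estimated from, so the reported odds ratio could depend on software defaults or on where the fitting routine stops. A hospital variance has only two levels behind it. When it is estimated at zero, the model becomes ordinary logistic regression with no hospital adjustment.

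Hospital matters because the two sites are in different states and usual care is left to the local treating team, so readmission rates may differ between them. Under the stated covariate rule, hospital is adjusted for only if it happens to look different between arms. Whether the primary analysis adjusts for site would then be decided after baseline data are seen.

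**Working it through.** **1. The plan's own figure.** Inputs from the sample-size section: 30% versus 47.5%, 173 per group, alpha 0.05 (two-sided assumed). The pooled proportion is 0.3875.
- Standard error under no difference: √(2 × 0.3875 × 0.6125 / 173) = 0.0524.
- Standard error under the planned difference: √((0.30 × 0.70 + 0.475 × 0.525) / 173) = 0.0515.
- Power: Φ((0.175 − 1.96 × 0.0524) / 0.0515) = 0.920.

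The 90% power requirement is 161 per group without continuity correction and exactly 173 with it. 346 / 0.8 = 432.5, against the stated 432. The figure reproduces as a two-proportion comparison, so a single yes/no value per patient is the plan's own planning basis.

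**2. Patient random intercept, one value per patient.** Take 52/173 versus 82/173 readmitted (0.30 × 173 = 51.9; 0.475 × 173 = 82.2). The marginal probability in an arm is ∫ expit(η + σu) φ(u) du. For any σ, some η reproduces the observed proportion exactly, so the maximised likelihood cannot depend on σ.

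| σ | Maximised log-likelihood | Odds ratio |
|---|---|---|
| 0 | −225.4444 | 0.477 |
| 0.5 | −225.4444 | 0.458 |
| 1 | −225.4444 | 0.411 |
| 2 | −225.4444 | 0.299 |
| 4 | −225.4444 | 0.135 |

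The data cannot choose between these rows.

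**3. Hospital random intercept, two hospitals.** Simulation with 346 patients split equally between two hospitals, 300 runs per scenario. The true log odds ratio is logit(0.30) − logit(0.475) = −0.747.

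| Assumed true hospital SD | Runs with estimated SD below 0.02 | Mean log odds ratio |
|---|---|---|
| 0 | 81% | −0.765 |
| 0.3 | 49% | −0.752 |
| 0.5 | 34% | −0.763 |

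The variance is often estimated at zero even when the hospitals differ. The treatment estimate stays close to the truth.

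**4. Size of chance site imbalance.** Assume unstratified 1:1 allocation and 216 patients per hospital. If a and b are the numbers allocated to intervention at each site, the between-arm gap in site share is approximately (a − b)/216. Its SD is √(54 + 54)/216 = 10.39/216 = 4.8 points, so the 95% limit is 1.96 × 4.8 = 9.4 points (9.3 by simulation). Multiplying 9.3% by the assumed difference in readmission rate between hospitals gives the shift in the crude treatment difference:

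| Assumed site gap | Shift at the 95% limit |
|---|---|
| 5 points | 0.5 points |
| 10 points | 0.9 points |
| 15 points | 1.4 points |
| 20 points | 1.9 points |

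The article gives no hospital-specific rates, hence the range.

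**5. Precision gained by always including hospital.** Assume a 15-point site gap, so each site lies 7.5 points either side of its arm mean. The within-site standard error is √((0.459375 − 2 × 0.075²) / 173) = 5.09 points, against 5.15 points crude (step 1). A simulation gave 5.20 falling to 5.09 points and power rising from about 91.3% to 92.0%, with no bias. If the sites do not differ, essentially nothing is lost.

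**The case against.** The strongest reply is that the article names a model class and no random effect, so the difficulty rests on a structure the reader supplies. Random-effect detail is commonly left to a full protocol or analysis plan. This stands in part. It rules out saying that the stated model is inestimable, but it does not explain why a mixed model is assigned to an outcome that the sample-size section treats as one proportion per arm.

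Readmission could also be modelled by interval, since patients are assessed at 1, 3 and 6 months, and a patient effect would then be estimable. That is possible. The Measures section does not exclude it, and the yes/no reading is inferred from the sample-size section.

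Four stronger readings are tempting and are not supported:

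- **A hospital effect cannot be estimated.** It is weakly estimated, with little harm to the treatment effect. Nor is hospital shown to be absent from the analysis: it may be the intended random effect, or may enter through the baseline-difference rule. Only its absence from the named covariates is established.
- **Randomisation ignores hospital.** The randomisation section is silent on stratification and does not say the sequence is unstratified. An article commonly omits such detail.
- **An odds ratio contradicts the powered difference in proportions.** Powering on two proportions and analysing with a logistic model is routine, and either model can be standardised to a risk difference.
- **Site imbalance could plausibly shift the result by 2 points at a 15-point site gap.** That needs both hospitals at opposite 95% limits, 122 and 94 of 216, a gap of 28/216 = 13 points in site share. A gap that large occurs in about 0.8% of trials.

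Finally, chance imbalance is not bias. It is already part of the crude difference's standard error of about 5.2 points. That is correct, and it is why the gain is one of precision and clarity.

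**Conclusion.** The point holds as a modest, cost-free improvement to a stated analysis. The model class assigned to the primary outcome does not fit the outcome as powered. On that reading a patient random effect is not identifiable, and a two-level hospital effect is poorly determined. Hospital, a plausible prognostic factor, is left to a data-dependent covariate rule.

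The benefit is small: less than one percentage point of power at an assumed 15-point site gap, and removal of chance shifts that are small beside the planned 17.5-point difference. The conclusion rests on reading the outcome as yes/no per patient and on two hospitals. The shift figures further assume equal enrolment and unstratified allocation. The sample size is unaffected.

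**What to change.** In the Data analysis section, or in the analysis plan before unblinding:

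- Define the primary outcome as at least one readmission by 6 months.
- Analyse it with ordinary logistic or binomial regression on treatment, age, gender and hospital, with hospital as a pre-specified fixed effect whether or not it looks imbalanced.
- Report the standardised risk difference with its 95% CI.
- Keep generalised linear mixed models for the secondary outcomes measured repeatedly, and name their random effects.

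The cost is a few sentences of wording. No additional patients or data are needed, and there is essentially no loss of precision if the hospitals turn out not to differ.

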### Ethical considerations

Ethical approvals and agreements have been obtained from all study sites and university settings involved in the study, specifically: Royal Brisbane and Women’s Hospital (Ref No RBWH HREC/14/QRBW/301), St Vincent’s Hospital Melbourne (Ref No: HREC-A 127/4), and Australian Catholic University (Ref No: 2014 309Q) Human Research Ethics Committees, as well as obtaining an approval by the Department of Human Services External Request Evaluation Committee (EREC) (Ref No: MI3435) for accessing healthcare related resource usage and costs from Medicare and Pharmaceutical Benefits Scheme (PBS) database. The trial may be audited according to the practices of the participating facilities at the discretion of their human research ethics committees or research governance offices. All ethical considerations including obtaining individual patient’s informed consent, emphasising voluntary participation, ensuring privacy and confidentiality, secure storage of data, and strict authorised personnel accessibility to the data will be strictly adhered to.

This study does not have a data monitoring committee as it is not a trial of a new drug or medical device. The intervention being trialled is designed to promote adherence to recommended disease management strategies during the transition from hospital to home. It is not anticipated that there will be any adverse events associated with participation in the trial; however, all trial personnel will be encouraged to report any potential adverse events that may occur during the trial through the usual hospital incident reporting systems, as well as to the trial investigators for review and reported directly to the human research ethics committee at the relevant participating site as well as notifying human research ethics committees at other sites.

This study protocol (version 1.01) has been prepared in compliance with the Helsinki Declaration, and has been prospectively registered with the Australia and New Zealand Clinical Trials Registry (ACTRN12614001317684). If any amendment to this trial protocol is required, investigator MC will be responsible for disseminating this information to trial personnel, and human research ethics committees at the participating sites. This study protocol has been prepared following the Standard Protocol Items: Recommendations for Interventional Trials (SPIRIT) guidelines. Trial findings will be reported through peer-reviewed publications with authorship determined in accordance with the International Committee of Medical Journal Editors recommendations.

## Discussion

It has been estimated that approximately 25% of patients with ACS have comorbid type 2 diabetes [24]. These patients have higher morbidity and mortality rates compared to those without diabetes, and have higher rehospitalisation rates [25]. Internationally, the proportion of patients hospitalised with ACS is likely to increase as a result of ageing populations [26] and the number of patients being diagnosed with type 2 diabetes is also rising [1–3, 24]. Higher projected incidence and prevalence of these conditions have made management of these diseases priority areas for research in many countries due to large potential personal and economic costs [1–3, 24, 25].

Evidence from prior research has indicated cardiac rehabilitation and diabetes self-management programs which include strategies for risk factor reduction, increasing physical activity and psychosocial management are beneficial in the management of these conditions and can subsequently decrease hospitalisations [27]. However, there is a paucity of literature reporting the comparative effectiveness of interventions addressing the needs of patients with dual diagnoses of ACS and type 2 diabetes who are transitioning to home after an acute hospital admission. Patients with both conditions may have insufficient adherence to treatment regimens and lower cardiac rehabilitation completion rates [28, 29] that may contribute to negative health events and avoidable hospital presesmntations.

Our previous randomised controlled trials undertaken in a general medical population of hospitalised older adults have demonstrated significant reductions in readmissions, improved quality of life and cost effectiveness through implementation of a theory based intervention comprising home visit and telephone follow up after discharge from hospital [8, 30]. Additionally, our previous work has addressed a number of gaps in the literature regarding needs of ACS patients with type 2 diabetes, and we have piloted cardiac-diabetes self-management programs in preparation for the present trial. Results from this preparatory work have demonstrated the feasibility of the program and a favourable effect on patient self-efficacy [12]. This proposed study builds on previous work through delivering an intervention prepared with a multidisciplinary team, to be evaluated in a randomised controlled trial across two states in Australia to evaluate the clinical and cost effectiveness of this cardiac-diabetes TRANSCARE program.

### Limitations and strengths

This study faces pragmatic challenges associated with investigator initiated trials delivering an intervention at more than one site, alongside administration-related challenges from multi-institutional collaboration. However, this may also be considered a strength of the study as the involvement of more than one study site may enhance the ability to generalise findings from the trial. The investigators have also taken steps to safeguard consistency in the conduct of the trial between sites by ensuring one person is responsible for training the research assistants for the trial, as well as the research nurses delivering the intervention. The same person is also the main contact point for any concerns that may arise during the trial regarding patient recruitment or data collection. Regular monitoring visits will be made throughout the trial to ensure consistency and integrity of the intervention is maintained. Another limitation of the trial pertains to uncertainty that has been described regarding the sample size due to the potential impact of restraints associated with the administration of grant funding, uncertain recruitment rates and no prior effect size data derived from a sample that is closely matched to the anticipated trial population. Instead, power calculations have been estimated for a maximum (target) sample size and possible smaller sample sizes that may occur based on the assumption of a more conservative effect than that observed from a similar intervention approach among hospitalised older adults (not targeted to ACS and diabetes).

## Conclusion

This study protocol has described a randomised trial that will evaluate an intervention program for patients with ACS and Type 2 diabetes commencing in an inpatient hospital setting and transitioning to the home environment. The theory-based intervention comprising face-to-face sessions and telephone follow up aims to increase self-efficacy to enhance self-management behaviours and thus improve health outcomes and reduce hospital readmissions.

## Abbreviations

ACS: Acute coronary syndrome
CDSMP: Cardiac-diabetes self-management program
OECD: The Organisation for Economic Co-operation and Development
RA: Research assistant
RCT: Randomised controlled trial
ResN: Research Nurse
STEMI: ST-segment elevation myocardial infarction.
